**Cost outcomes**		
Outcome 7	Cost of EDDIE+ implementation	The cost of implementing the EDDIE+ program will be measured by assigning profession specific wage rates, plus on-costs, to the duration of staff time associated with completing program activities (e.g. training, monitoring, facilitation). It will also include the costs of travel to sites, training materials and medical equipment.
Outcome 8	Cost of health service use	Health service costs to include ambulance transfers, ED presentations and hospital admissions.
**Process outcomes**		
Extent and fidelity of intervention (EDDIE+ program) implementation, impact, and contextual barriers and enablers of the EDDIE+ program		

### Data collection methods

#### Resident demographic and clinical data

Non-identifiable individual resident data at each RAC home will be extracted from the aged care provider’s existing routinely collected datasets. These will be used to report on the demographic characteristic summaries of the cohort to inform the generalisability of our results to other settings nationally and internationally. To review for seasonality and potential confounders over time we will use historical routinely collected data for residents at enrolled RAC homes for the two-year period directly before the trial start date.

#### Health services use and cost data

Non-identifiable individual resident data on transfer to and from EDs and admissions to hospital will be collected prospectively by the EDDIE+ facilitators based on resident care notes, with support from the project team. Data on monthly RAC home bed availability and occupancy rates will be used in calculating ED transfer and hospital admission rates.

To supplement the prospectively collected hospital transfer data, non-identifiable individual resident health service use and cost data will be retrospectively linked using state-level administrative datasets containing detailed information on ED and hospital diagnosis codes, length of stay, discharge outcomes and costs. These administrative data will be extracted using a data linkage process based on RAC home addresses for the dates of the trial period, as well as for a historical period of 2 years directly before the trial start date. Linked data will be validated against the prospectively collected ED and hospital transfer data from the enrolled RAC homes to ensure its accuracy.

#### Family awareness and experience survey activities

All current family members or nominated advocates of residents at enrolled sites will be invited to complete a short questionnaire on their awareness and experience of EDDIE+ at the end of the trial period. In addition, semi-structured interviews will be conducted with a purposive sample of family members or nominated advocates of residents both with and without an experience of hospital admission or proactive management of deterioration in the RAC home during the intervention exposure period. Interviews will be conducted until thematic saturation has been reached, up to a maximum of 30 interviews across the 12 sites.

#### Staff self-efficacy questionnaire

All nursing staff and personal care workers staff will be invited to complete a baseline measure of occupational self-efficacy using a validated questionnaire [19] to be administered immediately prior to staff training sessions. The self-efficacy questionnaire will be repeated in the final 2 weeks of the intervention exposure phase and up to 2 weeks post implementation.

#### Process evaluation

Process evaluation data will be collected using a series of templates based on i-PARIHS to guide the assessment of contextual barriers and enablers, conduct qualitative interviews with key stakeholders and undertake systematic implementation planning and record keeping.

Interview questions will focus on how the EDDIE+ program was introduced, any adaptations that were made, how staff responded, what changes in practice were implemented, and contextual factors that influenced implementation. Individuals from the following two stakeholder groups will be invited to voluntarily participate in a 30-min group or individual interview based on the i-PARIHS constructs: RAC home nursing staff and personal care workers; and, other RAC home stakeholders such as RAC home managers, EDDIE+ facilitators, Bolton Clarke executive management and health professionals who provide care to residents.

For each group, the participants will be purposively sampled to cover a representative cross section of stakeholder positions based on roles or interactions within the sites. Interviews will be conducted until thematic saturation has been reached, up to a maximum of 30 interviews for each stakeholder group across the 12 sites. Interviews will be conducted in the later stages of the implementation exposure phase up to 4 weeks post-trial.

### Data management

All research data will be stored on computer hard disk drives. These computers are networked to a password protected file storage server. The server has an automated daily batch back up procedure of the entire hard disk drive of each computer. Data will be shared via a password protected file storage server at the university leading the research that only members of the university-based project and investigator team can access. Data will be retained for a minimum of 15 years [20]. At the end of the study, final non-identifiable data sets will be deposited in a university Research Data Storage System. In line with publication embargoes and requirements, we will generate a document object identifier (DOI) for each non-identifiable data set and make these records publicly accessible.

### Sample size calculation

A simulation-based statistical power calculation was performed for the primary outcome of total hospital bed days. The simulations used a stepped-wedge design of 12 sites of 100 residents per site with 1 site switched from baseline phase to intervention exposure phase each month as shown in Fig. 1. The study design was estimated to have a 91% power to detect a 41% reduction in total bed days from a baseline period total hospital bed days of 346 bed days per 100 residents per year [12]. The power calculation was based on a 5% statistical significance level.

### Analysis

The time unit used in the analyses of Outcomes 1 to 4 is months. Data from the intervention introduction phase (phase 3) will not be in included in the statistical analyses but will instead inform the process evaluation. Subgroup analyses of Outcomes 1 to 6 will be performed for each RAC home separately. An initial analysis will be created using a scrambled intervention group by randomly allocating each RAC home to the baseline or intervention exposure period. A complete statistical report will be created using this scrambled data and sent to all investigators for discussion. This will allow investigators to query the methods and approaches used prior to the final report. It can also uncover errors in the code or data. Changes can be made prior to seeing the main results, which will help avoid the bias of only making changes where results are perceived as unfavourable.

There is a possibility that a disease outbreak (including COVID-19) could occur in one or more of the enrolled RAC homes during the study period. This may impact on hospital transfers and admissions and could potentially bias primary and secondary outcome findings. The analysis of Outcomes 1, 2, 3, 4 and 8 will therefore be conducted both with and without the inclusion of any outbreak related transfers and admissions.

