## Methods and design

### Study design

This study will adopt a stepped-wedge randomised controlled trial design (Fig. 1). Four phases will be sequentially rolled-out over 58-weeks: preparation; baseline (usual care) exposure; intervention introduction; and intervention exposure. The timing of the crossover from usual care to intervention introduction will be randomly allocated by the study statistician ([name]). Individual RAC homes will be notified of their intervention introduction date by the project team 10 weeks prior to commencement, to allow for adequate preparation time.

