### Analysis of primary outcome: Total number of hospital bed days

The primary outcome will be analysed using a mixed-effects Gamma regression model to estimate the impact of the EDDIE+ intervention while simultaneously accounting for RAC facility-specific variations in total hospital bed days. The key covariate will be the temporal indicator for the switch from baseline phase to intervention exposure phase, and the associated regression coefficient quantifies the change in total bed days associated with the EDDIE+ intervention period across all 12 RAC facilities. A linear time covariate in months since start of trial will be included in the regression model to capture any time trends in bed days that are not directly attributed to the intervention.

The regression model will also estimate RAC facility-specific random deviations from the overall baseline phase total hospital bed days from an RAC facility to account for any underlying differences at the different sites. It is possible that these random deviations are close to zero and the model fitting procedure may not converge. If this occurs, we will leave out the random intercept component and fit a standard Gamma regression model to the data.

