## Discussion

The EDDIE+ program is focussed on upskilling nursing staff and personal care workers within RAC homes so they can better recognise and manage early signs of deterioration in residents, with the aim of reducing unnecessary hospital admissions. Building upon previous pilot work, it will provide training, decision support tools, facilitation support and medical equipment with the aim of empowering staff to deliver safe and effective care within the residents’ home environment. The program is grounded in the principles of implementation science, with an emphasis on creating system-level and cultural change to support the program becoming embedded in business-as-usual practice.

The avoidance of unnecessary hospital admissions is expected to improve resident outcomes by reducing the stress of hospital transfers for residents and families, while also preventing the risk of hospital acquired complications. Reducing unnecessary hospital transfers and admissions would free up resources for patients with greater health care needs and may reduce net health system costs. RAC home staff are also expected to benefit from increased feelings of empowerment in their ability to proactively identify and manage early signs of resident deterioration.

The stepped-wedge study design has several strengths. The incremental roll-out of the program to one site at a time is practical to implement, mimics how the intervention might be implemented in practice across other RAC providers [25] and is well-suited to the evaluation of health service delivery interventions [26]. This design allows the nurse educator and broader study team to work closely with each RAC home during the intervention introduction phase.

Each RAC home contributes data to both the baseline and intervention exposure groups, mitigating risk associated with comparing heterogeneous settings. This crossover also means that temporal effects can be studied [27] with more efficiency than other cluster designs [28]. The main drawbacks of this design are the potential risk of secular trends unrelated to the intervention exposure, and risk of unequal exposure to seasonal trends. This could include exposure to a widespread outbreak, for example COVID-19, or the implementation of other hospital avoidance initiatives. These risks were taken into consideration in the statistical analysis plan.

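### Analysing each home separately makes the home-level results for Outcomes 1 to 4 uncontrolled before-after comparisons that cannot separate EDDIE+ from season

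*Protocol article*

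**What the plan says.** The Analysis section commits to home-level work: "Subgroup analyses of Outcomes 1 to 6 will be performed for each RAC home separately". It does not say which model is fitted within a home, whether hypotheses are tested, or what the results are for.

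The main analysis is different. For Outcome 1 it is one mixed-effects Gamma model with a switch indicator, a home random intercept and a time term; "the associated regression coefficient quantifies the change in total bed days associated with the EDDIE+ intervention period across all 12 RAC facilities". On time, the section on the primary outcome says "A linear time covariate in months since start of trial will be included in the regression model to capture any time trends in bed days". Outcomes 2 to 4 also have pooled mixed models with calendar month.

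On the layout, Study design says "Four phases will be sequentially rolled-out over 58-weeks", and Sample size calculation assumes "12 sites of 100 residents per site with 1 site switched from baseline phase to intervention exposure phase each month". Data from the introduction phase are left out of the statistical analyses.

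The Discussion lists, among the main drawbacks of the design, the "risk of unequal exposure to seasonal trends", and says that such risks were considered in the statistical analysis plan. The data collection section provides two years of historical data to review seasonality.

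**The concern.** A stepped-wedge design separates intervention from calendar time by comparing homes that have switched with homes that have not, in the same month. A home analysed alone loses that comparison. Randomisation fixes when a home switches, but it supplies no control inside the home. Over a trial of little more than a year, one home's baseline and exposure months fall in different parts of the year, so a seasonal rise or fall in bed days, transfers, admissions or length of stay enters the home's estimate directly.

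A linear month term borrowed from the pooled model does not cure this. Within one home it is strongly correlated with the switch, it cannot follow a seasonal curve, and it can enlarge the error.

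The months are also unevenly split. With one home switching each month, the earliest home has very few baseline months and the latest very few exposure months. At stake is the reading of differences between homes: apparent variation in effect may reflect switch date and noise.

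**Working it through.** **The plan's own figure.** "The study design was estimated to have a 91% power to detect a 41% reduction in total bed days". This cannot be reproduced, because the article gives no Gamma shape, CV or between-home variance. Working backwards with a two-sided 5% level, 91% power needs SE = 0.528 / (1.96 + 1.34) = 0.160. In a log-link approximation with switch, linear month and home intercepts, that corresponds to a home-month CV of about 0.47-0.59 (0.66-0.78 without intercepts). This serves only to judge the CV assumed below.

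**Inputs**
- Planned effect: a 41% reduction, log(0.59) = -0.53 (Sample size calculation).
- 12 homes, one switching per month (Sample size calculation).
- Length: 58 weeks is about 13.3 calendar months (Study design); 14 months assumed.
- Introduction phase: excluded (Analysis); its length is not in the text, one month assumed.
- Season: no amplitude in the article; a 12-month cosine on the log scale with amplitude 0.2 assumed, peak exp(0.2) = 1.22 times the average level.
- Home-month CV: 0.7 assumed.

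Under this layout home *k* has *k* baseline months and 13 − *k* exposure months.

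**Seasonal bias, no true effect.** Let *r* be the residual of the switch indicator after regression on a constant (crude), or on a constant and month (linear). The bias is Σ r·s / Σ r², with *s* the seasonal curve, taken at each home's worst phase.
- Crude: 0.20-0.22 across homes, a spurious ratio of exp(−0.20) = 0.82 to exp(−0.22) = 0.80.
- Linear month within the home: 0.41-0.53, a spurious ratio of exp(−0.41) = 0.66 to exp(−0.53) = 0.59.
- The opposite phase gives the same size with the other sign and would mask a real reduction.

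**One shared season.** Homes cannot each have their own worst phase. With a common phase and linear month, at most 2 of 12 homes have a bias of −0.5 or beyond, and biases differ in sign between homes.

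**Precision.** SE = CV / √(Σ r²); for the crude contrast this is CV·√(1/n₀ + 1/n₁).
- Crude: 0.7·√(1/6 + 1/7) = 0.39 for a middle home; 0.7·√(1/1 + 1/12) = 0.73 for the first or last.
- Linear month: Σ r² runs from 0.647 to 0.910, so SE = 0.7/√0.647 = 0.87 to 0.7/√0.910 = 0.73.
- A 95% interval extends by a factor of exp(1.96 × 0.39) = 2.1 to exp(1.96 × 0.73) = 4.2 each way crude, and 4.2 to exp(1.96 × 0.87) = 5.5 with linear month.

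**Sensitivity**
- With 13 or 14 months and 0 to 2 excluded months, the worst-phase bias with linear month ranges from 0.31 to 0.63.
- For a season expressed as a percentage of the mean, one home's crude ratio reaches 0.59 only at about ±40%; with linear month, ±17% to ±25% suffices in the most extreme home.
- At a CV of 0.573 (13 months, no gap), single-home power for a 41% reduction is 14%-38% crude and 12%-16% with linear month.
- The pooled model with home intercepts and linear month, under a ±20% season, gives a ratio of 0.96-1.04.

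**The case against.** The strongest reply is that these are labelled subgroup analyses, placed beside pooled models that estimate the effect of EDDIE+. A reader might infer that the trial itself is reduced to 12 before-after studies. The documents do not support that: the pooled models for Outcomes 1 to 4 remain, and for bed days the same calculation leaves the pooled estimate little changed.

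A reader might also infer that season would produce or erase a 41% reduction in every home. That does not follow. The amplitude is assumed, the larger bias needs a within-home linear term that the article does not specify, and one shared phase puts few homes near that size. Nor does the article say that home estimates will be fed back to homes or used to rank them; it promises results to each home without saying home-specific effects. Counting false positives over homes and outcomes would presume significance tests that are not stated.

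The quoted sentence is also wider than the criticism. Outcome 5 is collected only at the end of the trial and summarised descriptively, and Outcome 6 is a before-after comparison in the main plan already.

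Finally, seasonality is acknowledged, historical data are available, and further sensitivity analyses sit in a file not shown. That acknowledgement stands, but it does not give concurrent controls back to an analysis defined as separate for each home. That part is fixed in the text.

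**Conclusion.** The point holds for Outcomes 1 to 4 and for the home-level analyses only. A single home cannot separate EDDIE+ from calendar time, and this follows from the one-way crossover without any assumed figure. The size is conditional on 14 months, one excluded month, a log-amplitude of 0.2 and a CV of 0.7. On those assumptions the crude seasonal bias in one home can reach about 40% of the planned log effect (0.20-0.22 against 0.53), and with linear month fitted within the home it can approach the whole of it in a few homes. The imprecision remains even without season: at these standard errors most single-home estimates say little about a 41% reduction. The change is worth making, since it is cheap and leaves the primary analysis as planned.

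**What to change.** For Outcomes 1 to 4, replace the separate home analyses by home-specific effects from the pooled model. Add a random intervention effect by home, keep calendar-time terms shared by all homes, and report shrunken home ratios with intervals together with the between-home SD. Month terms rather than a straight line would let the shared part follow season. Show single-home data only as time plots with the switch marked, labelled descriptive. State in advance that if the random slope does not converge, the plots alone are reported; the article already foresees that even the random intercept may fail to converge.

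The cost is one extra random term in a supporting analysis. Home estimates will be pulled towards the average, and with 12 homes the between-home SD will be imprecise, which its interval should show.

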### Analysis of primary outcome: Total number of hospital bed days

The primary outcome will be analysed using a mixed-effects Gamma regression model to estimate the impact of the EDDIE+ intervention while simultaneously accounting for RAC facility-specific variations in total hospital bed days. The key covariate will be the temporal indicator for the switch from baseline phase to intervention exposure phase, and the associated regression coefficient quantifies the change in total bed days associated with the EDDIE+ intervention period across all 12 RAC facilities. A linear time covariate in months since start of trial will be included in the regression model to capture any time trends in bed days that are not directly attributed to the intervention.

The regression model will also estimate RAC facility-specific random deviations from the overall baseline phase total hospital bed days from an RAC facility to account for any underlying differences at the different sites. It is possible that these random deviations are close to zero and the model fitting procedure may not converge. If this occurs, we will leave out the random intercept component and fit a standard Gamma regression model to the data.

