**Effectiveness outcomes**		
Primary outcome (Outcome 1)	Number of hospital bed days	Total number of hospital bed days residents accrued during the baseline and intervention exposure periods, accounting for RAC home occupancy levels.
Outcome 2	Emergency Department (ED) transfer rates	Resident transfers to emergency departments including mode of transfer, diagnosis code, triage category, length of stay (mins) and discharge outcome.
Outcome 3	Hospital admission rates	Residents admitted to hospital as an inpatient (exclusive of dialysis admissions) including diagnosis code (Australian Refined Diagnosis Related Group (AR-DRG)) and mode of arrival.
Outcome 4	Length of hospital stay and discharge outcome	Time (in days/hours) from admission to discharge for each episode of care including diagnosis code, time in intensive care unit and discharge outcomes.
Outcome 5	Family awareness and experience	Family or nominated advocate responses to a short questionnaire and/or interview to ascertain awareness of EDDIE+ and family perceptions and experiences of the program.
Outcome 6	Staff self-efficacy	Staff scores on the Job-related and Group-related Self-Efficacy measure [19]

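### The primary Gamma model has no valid likelihood for a home-month with zero bed days, and it names no occupancy term although Table 1 requires one

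*Protocol article*

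**What the plan says.** The section on the primary outcome analysis fixes the model family: "The primary outcome will be analysed using a mixed-effects Gamma regression model to estimate the impact of the EDDIE+ intervention". The Analysis section sets the row: "The time unit used in the analyses of Outcomes 1 to 4 is months". The named terms are the intervention switch, a home-level random intercept and time ("A linear time covariate in months since start of trial will be included in the regression model"). The estimand is described as follows: "the associated regression coefficient quantifies the change in total bed days associated with the EDDIE+ intervention period across all 12 RAC facilities". If the random intercept prevents convergence, "we will leave out the random intercept component and fit a standard Gamma regression model to the data". The text does not say what happens to a month with no bed days.

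Table 1 defines Outcome 1 as "Total number of hospital bed days residents accrued during the baseline and intervention exposure periods, accounting for RAC home occupancy levels". The primary analysis section names no offset, denominator or occupancy covariate. The section on secondary outcomes does state a resident-day offset, for Outcomes 2 and 3. The section on health services use says: "Data on monthly RAC home bed availability and occupancy rates will be used in calculating ED transfer and hospital admission rates". Bed days are not mentioned there.

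**The concern.** There are two separate issues.

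**Zeros.** The Gamma distribution covers strictly positive values only. A month in which no resident of a home was in hospital is a legitimate observation and the kind of month the programme hopes to produce, yet the planned model cannot use it. The analyst would have to delete the month, add an arbitrary constant or change the model. Zero months should be commoner under the intervention, so deletion removes favourable intervention months and pulls the ratio towards 1.

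**Occupancy.** The outcome definition requires adjustment for occupancy, but the model as written estimates a change in raw bed days. If the number of filled beds changes when a home switches, the change is read as an intervention effect.

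**Working it through.** **The plan's own figure.** The sample size section gives 91% power for a 41% reduction from 346 bed days per 100 residents per year. Wald power for a log-link Gamma model (effect log 0.59; two-sided 5% assumed; 12 homes, one switch per month, linear time, 13 months with one introduction month) reaches 91% if the monthly coefficient of variation is about 0.51 with home effects, or 0.72 without. The article gives no variance, so 91% is attainable but cannot be verified.

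**1. Likelihood at zero.** With shape k, the Gamma log-density contains (k − 1) log y, which is infinite at y = 0 unless k = 1. R, the planned software, rejects a non-positive response in both the ordinary and the mixed Gamma fit. A test fit in Python returned an infinite log-likelihood. The fallback has the same support.

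**2. Chance of a zero month.** Inputs:
- Mean bed days per 100-resident home-month: 346/12 = 28.83 at baseline; 28.83 × 0.59 = 17.01 after a 41% reduction.
- Home-months: 12 × 13 = 156, less one introduction month per home (length assumed) = 144. With one switch per month these split into 1 + 2 + … + 12 = 78 baseline and 0 + 1 + … + 11 = 66 exposure months.
- Mean stay L: not given for this trial. The Background implies 160,000/27,000 = 5.93 days for potentially preventable admissions nationally. I use this as an assumption, with 4 and 8 days as a range.

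With Poisson admissions and bed days counted by calendar day, P(zero) = exp(−(A + H)). A is admissions per month (28.83/L at baseline) and H is the mean number in hospital at the start of the month (monthly bed days/30.4).

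At L = 5.93:
- Baseline: A = 4.87, H = 0.95, P(zero) = exp(−5.81) = 0.0030.
- Exposure, 41% reduction wholly through admissions: A = 2.87, H = 0.56, P(zero) = exp(−3.43) = 0.0324.
- Expected zero months: 78 × 0.0030 + 66 × 0.0324 = 2.4.
- P(at least one) = 1 − (1 − 0.0030)^78 × (1 − 0.0324)^66 = 91%.

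Chance of at least one zero month:

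| Scenario | 4 days | 5.93 days | 8 days |
|---|---|---|---|
| No effect | 4% | 35% | 78% |
| 41% reduction, all through length of stay | 5% | 41% | 84% |
| 41% reduction, split evenly | 16% | 68% | 96% |
| 41% reduction, all through admissions | 43% | 91% | nearly 100% |

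A 20% reduction at 5.93 days gives 38 to 58%.

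**3. Effect of dropping zero months.** I used simulated compound-Poisson bed days with 100 residents per home, between-home SD 0.2 (assumed), a true ratio of 0.59 acting through admissions, and home effects fitted as fixed.

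| Mean stay | Mean zero months of 144 | Gamma, zeros dropped: ratio (power) | Quasi-Poisson, zeros kept: ratio (power) |
|---|---|---|---|
| 5 days | 3.1 | 0.603 (72%) | 0.590 (77%) |
| 6 days | 5.5 | 0.615 (61%) | 0.587 (68%) |
| 8 days | 11.2 | 0.650 (41%) | 0.594 (54%) |

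The simulation credits all days to the month of admission. That yields more zeros than calendar-day counting (2.4 expected by calendar day in the worked case above), so these shifts lie towards the upper end.

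**4. Occupancy without an offset, no true effect.** Ratio estimated with home effects, linear time and the switch:

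| Occupancy pattern | Ratio |
|---|---|
| 10% fall that tracks each home's exposure | 0.90 |
| Fall shared by all homes (linear, step or three-month dip) | 0.998 to 1.002 |
| Home-specific drifts, SD 10% over the trial | 0.97 to 1.03 (central 95%) |

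With a log-occupancy offset, the first case returns 1.00 in the quasi-Poisson simulation.

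**The case against.** The strongest defence of the zero handling is procedural. The Analysis section commits to a full report on scrambled allocation before the main results are seen, partly to find errors, and allows changes at that stage. A zero in a Gamma fit would normally surface there, when any change could not be driven by the results. That stands as a real safeguard, but no replacement model is named, so the primary analysis would be chosen after inspecting the outcome data. Residual checks and sensitivity analyses are in Additional file 3, which is not shown. They may deal with zeros but would not alter the primary model fixed in the text.

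On occupancy, the response may be meant as bed days already scaled by occupancy. Table 1 can be read that way, and the sample size section gives its baseline rate per 100 residents. On that reading the occupancy point falls away. Against it, the primary analysis section speaks of total bed days throughout, and the article states a resident-day offset where it intends one. Scaling would not help with zeros in any case. A reader might also infer that occupancy data are reserved for ED transfer and admission rates. The text names those uses but does not exclude others.

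The input for length of stay is soft: 5.93 days describes potentially preventable admissions, while the outcome covers all bed days. Home sizes are not given. Smaller homes have lower selection priority but are not excluded, and they would produce more zeros.

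**Conclusion.** The point holds as a wrong choice of family for the primary model and a mismatch between the outcome definition and the model. Both can be read from the article without any assumption.

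The size is moderate and conditional. A reader might infer that the primary fit will probably fail. The figures do not support that across the range: at a 5.9-day stay the chance of any zero month is 68 to 91% if at least half of a 41% reduction acts through admissions, but 35% if there is no effect, and it stays below one half at 4 days. When zeros occur they are few, and deleting them understates benefit and costs some power rather than creating a false positive.

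A reader might also infer that any fall in occupancy would pass for an effect. It would not: trends shared by all homes are almost fully absorbed by the time term and the staggered design. Material bias needs a change aligned with each home's switch, whose timing is randomised. The offset therefore mainly makes the model match Table 1 and guards against home-specific drift.

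Nor do the simulated powers below 91% show that the trial is underpowered. They rest on an assumed variance that the article does not state.

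**What to change.** For Outcome 1, prespecify a mixed-effects log-link model that admits zeros (negative binomial or Tweedie), with log(occupied resident-days in the home-month) as offset. Keep the intervention, linear time and home random-intercept terms. Report bed days per 1000 resident-days, the scale already used for Outcomes 2 and 3. Replace the standard Gamma fallback with the same zero-admitting model without the random intercept. Add bed days to the stated uses of the occupancy data, so that Table 1, the data section and the analysis section agree.

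The cost is revised analysis text and code. No new data are needed, because monthly occupancy is already to be collected. The power simulation should be re-run under the new model with its variance assumptions stated, and the result may be below 91%.
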